## Abstract

**Background:**

Benzamide-based radioligands targeting melanin were first developed for imaging melanoma and then for therapeutic purpose with targeted radionuclide therapy (TRT).

[^131^I]ICF01012 presents a highly favorable pharmacokinetics profile in vivo for therapy. Tumour growth reduction and increase survival have been established in preclinical models of melanoma. According the these preclinical results, we initiate a first-in-human study aimed to determine the recommended dose of [^131^I]ICF01012 to administer for the treatment of patients with pigmented metastatic melanoma.

**Methods:**

The MELRIV-1 trial is an open-label, multicentric, dose-escalation phase I trial. The study is divided in 2 steps, a selection part with an IV injection of low activity of [^131^I]ICF01012 (185 MBq at D0) to select patients who might benefit from [^131^I]ICF01012 TRT in therapeutic part, i.e. patient presenting at least one tumour lesion with [^131^I]ICF01012 uptake and an acceptable personalized dosimetry to critical organs (liver, kidney, lung and retina). According to dose escalation scheme driven by a Continual Reassessment Method (CRM) design, a single therapeutic injection of 800 MBq/m^2^, or 1600 MBq/m^2^, or 2700 MBq/m^2^ or 4000 MBq/m^2^ of [^131^I]ICF01012 will be administered at D11 (± 4 days). The primary endpoint is the recommended therapeutic dose of [^131^I]ICF01012, with DLT defined as any grade 3-4 NCI-CT toxicity during the 6 weeks following therapeutic dose. Safety, pharmacokinetic, biodistribution (using planar whole body and SPECT-CT acquisitions), sensitivity / specificity of [^131^I]ICF01012, and therapeutic efficacy will be assessed as secondary objectives. Patients who received therapeutic injection will be followed until 3 months after TRT. Since 6 to 18 patients are needed for the therapeutic part, up to 36 patients will be enrolled in the selection part.

**Discussion:**

This study is a first-in-human trial evaluating the [^131^I]ICF01012 TRT in metastatic malignant melanomas with a diagnostic dose of the [^131^I]ICF01012 to select the patients who may benefit from a therapeutic dose of [^131^I]ICF01012, with at least one tumor lesion with [^131^I]ICF01012 uptake and an acceptable AD to healthy organ.

**Trial registration:**

Clinicaltrials.gov: NCT03784625. Registered on December 24, 2018.

Identifier in French National Agency for the Safety of Medicines and Health Products (ANSM): N°EudraCT 2016-002444-17.

## Background

Melanoma is a cancer arising from skin melanocytes but mucosal or uveal forms exist [1]. Surgical excision represents the first-line treatment for melanoma [2]. Depending on TNM staging, adjuvant immunotherapy or targeted therapy could be proposed to lower the metastatic risk [3]. However, melanoma is a highly metastatic cancer and represents a major public health problem for many years. Until 2010, only chemotherapies were available to treat metastatic melanomas and prognostic was poor [4]. MAPK pathway targeted therapies including BRAF V600E [5] and MEK-activated proteins [6] and immunotherapies with antibody against immune check-point inhibitors such as CTLA-4 [4], PD-1 [7] and its ligand PD-L1, have completely modified metastatic melanoma prognosis. However, patients can be non-responders or develop some resistance [8]. Therefore, it is still mandatory to develop new therapeutic strategies as external stereotactic radiation therapy, alone or combined with systemic treatments. Targeted radionuclide therapy (TRT) [9], a nuclear medicine strategy that consists in administering a radiopharmaceutical compound to the patient in order to deliver a high absorbed dose of radiation to tumours while avoiding or minimizing normal tissue toxicities, could be one of them.

Multiples approaches have been developed in this field [9, 10], using melanin targeting by antibodies or small molecules (benzamides), or MSH analogs (peptides), or membrane receptors targeting (antibodies). A few have been tested in human with mixed results [9, 10]. Only a phase I trial has tested a benzamide radiolabeled with iodine-131 on a series of 26 patients with metastatic malignant melanoma [11]. All received a diagnostic dose of 235 ± 62 MBq of [^123^I]-BA52 for planar and SPECT/CT imaging, and only 9 patients were selected to receive a radionuclide therapy with a single dose of [^131^] I-BA52 with different activity levels between 510 to 6600 MBq. A specific uptake and long-term retention in tumor tissue with low transient uptake in the excretory organs was observed with diagnostic injection of [^123^] I-BA52. The highest estimated dose to a normal organ was found for the lung (mean, 3.1 Gy/GBq). No relevant acute or mid-term toxicity was observed with the administered doses. In tumor tissue, a maximum dose of 12.2 Gy per GBq of [^131^] I-BA52 was calculated. Among the 5 patients who received [^131^] I-BA52 dose > 4.3 GBq (potentially effective), 3 demonstrated a surprisingly long survival of more than 2 years. These results highlight the potential of small molecule with high melanin affinity for TRT to treated metastatic melanoma.

Since 1990’s, our team has developed several compounds displaying a high affinity for melanin, benzamide-derived melanin-targeting molecules for imaging and/or therapy [12–14]. BZA and BZA2 radiolabeled with iodine-123 have been clinically tested for a diagnostic approach for SPECT imaging of metastatic melanoma leading to phase II clinical trials [15, 16]. In a prospective and multicentric phase III clinical study comparing [^123^I]BZA2 scintigraphy to [^18^F]-FDG PET-CT for melanoma staging (*n* = 87), the sensitivity and specificity of BZA2 for the diagnosis of pigmented lesions were 85 and 76% [17].

ICF01012 is a pharmacomodulated form of this BZA2, with highly favorable pharmacokinetics in murine models for therapy, with a long-lasting tumoral intake (8 days) and a rapid elimination of non-target organs (< 24 h) [18]. The TRT efficiency of [^131^I]ICF01012 have been achieved on syngeneic murine models (B16F0 and B16Bl6) and murine model bearing xenografts (SK-Mel 3). With single or multiple injection of [^131^I]ICF01012, a slowing of tumor growth and an increase in survival were observed [19–21]. A clear relationship between the presence of melanins and the efficacy of therapy has also been demonstrated. Radiotoxicity studies conducted with [^131^I]ICF01012 at a therapeutic dose on highly pigmented mouse models have shown a transient decrease in white blood cells and a relative decrease in the thickness of the retina [22]. Dosimetry extrapolations have shown retina-values below the maximum tolerated doses, suggesting that this ocular specific targeting is not expected to have an impact in human [23]. Furthermore, preliminary toxicological studies point out that TRT with [^131^I]ICF01012 was compatible with clinical requirements. Impact of TRT using [^131^I]ICF01012 has also been evaluated on metastasis mechanisms [24] and current melanoma treatments (immune checkpoints inhibitors [25] and MAPK targeted therapies [26]) in murine melanoma models.

According to these preclinical results, [^131^I]ICF01012 could be a promising theranostic approach with a first diagnostic dose of [^131^I]ICF01012 (low activity) for pre-selected melanin positive melanoma patients who might benefit from this [^131^I]ICF01012 TRT (therapeutic activity). The MELRIV-1 trial is a first-in-human study aimed to determine the recommended dose of [^131^I]ICF01012 to administer for the treatment of patients with pigmented metastatic melanoma (binding [^131^I]ICF01012).

## Methods/design

### Study design

This is an open-label, multicentric, “first-in-human”, dose-escalation phase I trial of a radiopharmaceutical.

The study based on a theranostic approach is divided in 2 steps:Firstly, a “selection part”, to determine if the patient is eligible for therapy, i.e., if the radiopharmaceutical is up-taken by metastases. During this phase, a single IV injection of low activity of [^131^I]ICF01012, called “diagnostic dose” will be injected to the patient. Pre-treatment dosimetry allows to measure for each patient the absorbed dose by organs and tissues. Patients will be eligible for the second step, the “therapeutic part” if they present at least one tumor lesion with [^131^I]ICF01012 uptake and if mean absorbed dose (AD) to liver < 26 Gy, kidney AD < 16.2 Gy, lung AD < 15 Gy et retina AD < 40 Gy.Secondly, a “therapeutic part” consisting of a single IV injection of [^131^I]ICF01012 at a therapeutic activity. The dose escalation will be driven by a Continual Reassessment Method (CRM) [27] with 4 [^131^I]ICF01012 activity levels: 800, 1600, 2700, or 4000 MBq/m^2^.

The duration of intervention for each patient will be 7 days (diagnostic phase only) or 3 weeks (diagnostic phase + therapeutic phase). Follow-up will last 4 weeks (diagnostic phase only) or 10 weeks (diagnostic phase + therapeutic phase).

### Coordination and participating institutions

The Centre Jean Perrin is the sponsor and responsible for the coordination of the trial, data management, monitoring and statistical analysis.

The multicenter study is currently conducted at 2 sites in France: the University Hospital of Clermont-Ferrand and the Centre Jean Perrin. Patients with cutaneous melanomas will be recruited at the Dermatology and Oncodermatology Department of the University Hospital of Clermont-Ferrand and patients with uveal melanomas will be recruited at the Jean Perrin Cancer Center. For all patients, targeted radionuclide therapy will be performed at the Nuclear Medicine Department of the Jean Perrin Cancer.

### Objectives and endpoints

#### Main objective

The primary objective is to determine the recommended dose of [^131^I]ICF01012 to use for pigmented melanoma metastases TRT.

The primary endpoint is the recommended therapeutic dose of [^131^I]ICF01012, defined as the higher dose for which the percentage of dose-limiting toxicity (DLT) is lower than 33%. DLT is defined as any grade 3-4 NCI-CT toxicity, except for alopecia, nausea and vomiting or fever, which can be managed by symptomatic treatment. Only toxicities experienced during the 6 weeks following therapeutic dose administration will be considered as DLT.

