#### Secondary objectives

The secondary objectives and the corresponding end-points are:To determine the [^131^I]ICF01012 sensitivity and specificity in a patient-based analysis and in a lesion-based analysis.[^131^I]ICF01012 sensitivity and specificity in patient-based analysis and in lesion-based analysis will be quantified by comparison of visualized or non-visualized lesions with [^131^I]ICF01012 imaging compared to metastatic lesions objectified by standard imagery (TEP-TDM or TDM) and or clinical evaluation.To evaluate the tolerance of [^131^I]ICF01012. [^131^I]ICF01012 tolerance (acute and delayed toxicities) will be evaluated with the Common Terminology Criteria for Adverse Events (CTCAE, version 4.03) with a special consideration for skin-related, ocular and neurological toxicities. Tolerance assessments include: Clinical examination with vitals (heart rate, blood pressure, temperature, respiratory rate), weight, height, OMS performance status; Cardiac evaluation (myocardial perfusion scintigraphy with measure of left ventricular ejection fraction (LVEF), Electrocardiogram (ECG); Specialised consultation with dermatologist, neurologist and ophthalmologist (with of a dilated fundus examination); Blood test including Fool blood count, prothrombine time, factor V, sodium, potassium, chloride, calcium, phosphore, bicarbonate, serum total protein, serum albumin, fasting blood glucose level, Thyroid-stimulating hormone (TSH), free thyoroxine (fT4), free triiodothyronine (fT3), creatinine, urea, bilirubin, Alkaline phosphatase (ALP), Gamma-glutamyltransferase (GGT), Aspartate amino transferase (AST or SGOT), Alanine amino transferase (ALT or SGPT), Troponin Lactate dehydrogenase (LDH); 24-h urine collection tests: glucose, urea, creatinine, albumin, sodium, potassium, magnesium, calcium, protein electrophoresis. Reporting of serious adverse events and suspected unexpected serious adverse reaction will be carried out according to the local regulations.To evaluate the pharmacokinetics of [^131^I]ICF01012 including the study of biodistribution and excretion.Variations of [^131^I]ICF01012 radioactivity concentration (AUC, Tmax and Cmax) will be measured on whole blood plasma during 8 days after diagnostic dose. Plasmatic free fraction of [^131^I]ICF01012 will be quantified by radioactive counting for each patient.24-h urinary excretion will be measured by counting.The biodistribution will be assessed with planar scintigraphy by measuring the percentage of [^131^I]ICF01012 injected dose absorbed by target and non-target organs for both diagnostic and therapeutic doses.To assess the therapeutic response of [^131^I]ICF01012. Therapeutic response (objective response rate, rate of clinical benefit, progression-free survival) will be assessed by TDM according to RECIST 1.1 criteria and by [^18^F] FDG TEP/TDM according to PERCIST criteria.To evaluate the correlation between therapeutic response, injected dose and tumoral uptake.To evaluate the personalized dosimetry applied to [^131^I]ICF01012, and its interindividual variability, Absorbed dose for each organ will be assessed by MIRD formalism.To compare the therapeutic recommended dose with the dose calculated with personalized dosimetry;To compare biodistribution of diagnostic dose and therapeutic dose.

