#### Data analysis

Due to the nature and the design of the study, statistical analysis will be mainly descriptive. Two populations will be analyzed: the diagnostic population (all participants who receive the diagnostic dose) and the therapeutic population (all participants who receive the therapeutic dose). The recommended therapeutic dose will be defined as the highest tested dose for which the percentage of DLT in the diagnostic population is lower than 33%. DLT percentage will be calculated for each tested dose. Only therapeutic population will be included in the analysis of DLT and the efficacy analysis. The statistical significance threshold is set at 5%. Statistical analyses will be performed using R software.

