### Independent data monitoring Committee (IDMC)

IDMC will be set up to assess the progress of the clinical trial, safety data, benefit/risk ratio of the trial and to recommend to the Sponsor whether to continue, modify, or stop the trial. Members composing the IDMC will be selected to have the relevant clinical trials/medical expertise without direct involvement in the conduct of the trial. The committee will include a nuclear physician and 2 oncologists. Given the very low number of expected DLT and the use of a CRM, the committee will meet for each observed DLT or every 5 patients treated at therapeutic dose in absence of DLT.

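### The DLT definition covers grades 3-4 only, so a toxicity recorded only as grade 5 would not count as a DLT on the literal text

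*Protocol article*

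**What the plan says.** The Main objective section defines the endpoint by grade: "DLT is defined as any grade 3-4 NCI-CT toxicity, except for alopecia, nausea and vomiting or fever". It then sets the window: "Only toxicities experienced during the 6 weeks following therapeutic dose administration will be considered as DLT". The Methods paragraph of the abstract repeats the grade range: "DLT defined as any grade 3-4 NCI-CT toxicity during the 6 weeks following therapeutic dose".

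The recommended dose is "defined as the higher dose for which the percentage of dose-limiting toxicity (DLT) is lower than 33" per cent. On who is analysed, the Data analysis section says: "Only therapeutic population will be included in the analysis of DLT and the efficacy analysis". That population is everyone who receives the therapeutic dose, and the article gives no exclusion or replacement for a patient who dies.

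The Secondary objectives section names CTCAE version 4.03 as the grading scale. The IDMC section says that "the committee will meet for each observed DLT or every 5 patients treated at therapeutic dose in absence of DLT". No section names grade 5, fatal toxicity or treatment-related death as a DLT.

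**The concern.** The upper bound is closed. On CTCAE a death related to an adverse event is grade 5, which lies outside grades 3-4. The definition lists its exceptions and sets a time window, so it reads as the operative rule and not as shorthand. Applied as written, the most severe toxicity possible is missing from the numerator of the primary endpoint.

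Three uses of the DLT depend on this wording: the 33% rule that selects the recommended dose, the toxicity outcome fed to the CRM, and the event that triggers an IDMC meeting. Cohorts are of one patient and the recommended dose may rest on as few as six, so the classification of a single patient can decide the result.

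**Working it through.** **Inputs from the protocol article.** DLT grades 3-4 and six-week window (Main objective). Limit below 33% (Main objective, Data analysis). Cohorts of one, at least 6 patients at the recommended dose, 6 to 18 treated, 50% eligible for therapy (Sample size). Denominator: all who receive the therapeutic dose (Data analysis).

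**The plan's own figure.** Selection-part enrolment = treated / 0.50: 6 / 0.50 = 12 and 18 / 0.50 = 36. The stated 12 to 36 is reproduced. It does not depend on the DLT definition.

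**Effect on the 33% rule.** A dose passes if DLTs / n < 0.33.

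- n = 6: 1/6 = 16.7% passes and 2/6 = 33.3% fails, so at most one DLT is allowed.
- One grade 3-4 event plus one toxicity recorded only as grade 5: as written 1/6, passes; with the death counted 2/6, fails.
- The same reversal occurs at other sizes when the count is at the boundary: 2/7 = 28.6% against 3/7 = 42.9%, and 2/9 = 22.2% against 3/9 = 33.3%.
- In a cohort of one, the patient is 0/1 as written and 1/1 if counted.

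**How often a dose would pass at n = 6.** Let p be the true probability of a grade 3-5 toxicity and f the share of those recorded only as grade 5. Both are assumptions; the article gives neither. With q = p if grade 5 counts and q = p(1 − f) as written, P(pass) = (1 − q)^6 + 6q(1 − q)^5. For p = 0.40 with grade 5 counted: 0.6^6 + 6 × 0.4 × 0.6^5 = 0.0467 + 0.1866 = 0.233.

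| p | grade 5 counted | as written, f = 10% | f = 25% | f = 50% |
|---|---|---|---|---|
| 0.20 | 0.655 | 0.704 | 0.776 | 0.886 |
| 0.33 | 0.358 | 0.427 | 0.540 | 0.741 |
| 0.40 | 0.233 | 0.301 | 0.420 | 0.655 |

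**Effect on the CRM (illustration only).** The article does not give the model. I assumed a one-parameter power model, a normal prior with variance 1.34, a target of 0.33, four different skeletons and no limit on skipping levels. Suppose the first patient, at level 1, has no DLT and the second, at level 2, has a fatal toxicity. If the death is ignored, the model points to level 4; if it is counted, to level 1. This holds under all four skeletons.

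**Effect on the IDMC trigger.** A toxicity recorded only as grade 5 is not a DLT as defined, so it does not by itself meet the stated DLT trigger. The scheduled meeting after every five treated patients remains.

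**The case against.** The strongest reply is that the sponsor very probably means grade 3 or higher, and that the approved protocol, which the article condenses and which is not shown, may deal with deaths in the window. That is likely, but the article does more than leave a detail out: it states a bounded rule in two places.

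Several narrower objections stand:

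- **The gap is limited.** A patient who has a recorded grade 3-4 toxicity in the window and then dies already counts. Table 2 schedules physical examinations at D12, D13, D15, D16, D18 and D25, and haematology at D15, D16, D18, D25, D39 and D53, so many evolving toxicities would be recorded at grade 3-4 first. A reader might infer that every toxic death escapes the endpoint; the text does not support that.
- **Entry into the CRM as DLT-free is inferred.** It follows from the definition and the all-treated population, but neither the model nor any evaluability rule is shown. It should not be stated as what the trial does.
- **Unexamined escalation after a toxic death is unlikely.** Serious adverse events are reported under local regulations, and the IDMC reviews safety and may recommend changing or stopping the trial. Neither provision turns the death into a DLT, but both would bring it to attention.
- **The numerical case is constructed.** The 1/6 against 2/6 example sits on the boundary, and the shares and rates in the table are assumed. The IDMC section expects very few DLTs.
- **Attribution matters.** Patients have metastatic disease after failure of recommended treatments, and the life-expectancy criterion is only more than 3 months. Deaths from progression within six weeks are foreseeable and should not become DLTs merely because grade 5 is named.

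**Conclusion.** The point holds in limited form. On the literal text, a toxicity recorded only as grade 5, with no separate grade 3-4 toxicity in the six-week window, is not a DLT, yet the patient remains in the denominator. At six patients this can reverse the primary decision, from 33.3% (fails) to 16.7% (passes). The conclusion rests on the wording given in both places and on NCI-CT toxicity in the definition meaning the CTCAE scale named elsewhere.

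The CRM consequence is an inference, and the probabilities depend on assumed rates. Nothing suggests that the sponsor chose to leave deaths out. This is a wording defect, but in the primary endpoint of a first-in-human trial, where one patient can change the result.

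The Data analysis section also has a sentence that computes the DLT percentage in the diagnostic population, against its own sentence on the therapeutic population. A treated patient who dies is in the denominator under either, so this point is unaffected.

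**What to change.** In the Main objective section and in the abstract, replace the grade range with: *grade 3 or higher, including grade 5, that is, death related to toxicity and not to disease progression*. Keep the exceptions and the six-week window as they stand. The 33% rule, the CRM input and the IDMC trigger all refer to DLT, so they follow without further edits.

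The cost is small but not nil. The observed DLT rate may be higher, and each death in the window needs a judgement on whether it was due to toxicity or to progression. Enrolment of 12 to 36, the activity levels and the visit schedule do not change.

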##### Follow-up

Non-eligible patients for therapeutic part will be followed during 3 weeks: 2 follow-up visits are scheduled 14 days and 35 days after diagnostic dose injection for safety evaluation (clinical examination, vital measurement, blood and urinary analyses, specialized consultations (ophthalmologist, neurologist and dermatologist)).

For patient receiving the therapeutic dose, five follow-up visits are scheduled 14, 28, 42, 63 and 85 days after therapeutic dose injection. Each visit will include: clinical examination, vital measurement, blood and urinary analyses. Specialized consultations (ophthalmologist, neurologist and dermatologist) will occur 14 days after therapeutic dose and for dermatologist consultations 42 and 85 after therapeutic dose. Dosimetric acquisitions will be done on 14 and 63 after therapeutic dose (see below). Post-therapeutic cardiac evaluation (myocardial perfusion scintigraphy) and disease staging (cranial and thoraco-abdominopelvic CT scan and [^18^F] FDG PET-CT) will be done 85 days after therapeutic dose.

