## Discussion

The MELRIV-1 trial is the first in human evaluation of the [^131^I]ICF01012 TRT in metastatic malignant melanomas. This study aims to determine the recommended dose of [^131^I]ICF01012 to administer for the treatment of patients with pigmented metastatic melanoma (binding [^131^I]ICF01012).

[^131^I]ICF01012 is a melanin-targeting compound allowing both imaging and TRT [18]. Even though targeting melanin to destroy melanoma cells is a seducing approach, some concerns exist and have been taken in account for this study design. Firstly, melanoma cells can lose the ability to synthesize melanin during the dedifferentiation process [30]. BZA2 phase 3 studies showed that approximately 50% of metastatic lesions did not capture melanin radiotracer [17]. Secondly, melanin is also present in healthy organs and tissues, as skin (keratinocytes, nævi), eyes (retinal pigment epithelium), brain (basal ganglia), heart, and adipose tissues (morbid obesity) [31]. Moreover, classically, radiation sensitive organs in TRT are red bone marrow, kidneys and liver. A radiosensitivity inter-patient variation of 20% dose can exist [32].

The design chosen in this trial was based on a theranostic approach with a pre-treatment dosimetry, with an infra-therapeutic dose of the [^131^I]ICF01012 that permits to select the patients who may benefit of a therapeutic dose of [^131^I]ICF01012, with at least one tumour lesion with [^131^I]ICF01012 uptake and an acceptable AD to healthy organ. Radiotoxicity must be minimized with a pre-treatment dosimetry. A precise dosimetry, i.e. the quantification of energy deposed in tumour and non-target organs, is the main concern for TRT evaluation in a clinical trial [21, 23].

The used of radiolabelled benzamides may constitute a therapeutic solution for melanomas resistant to therapy (for review see [10]). Compared to external radiation beam therapy, TRT allows a systemic treatment of a polymetastatic disease. [^131^I]ICF01012 is an original strategy for targeting pigmented lesions, but also unpigmented metastases through a potential abscopal effect [25].

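### The recommended dose rests on 6-week toxicity alone, and no stated step brings severe toxicity found between week 6 and day 85 into the decision

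*Protocol article*

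**What the plan says.** The Main objective section of the protocol article makes the recommended therapeutic dose the primary endpoint, "defined as the higher dose for which the percentage of dose-limiting toxicity (DLT) is lower than 33" per cent. On severity, "DLT is defined as any grade 3-4 NCI-CT toxicity, except for alopecia, nausea and vomiting or fever", where these can be managed symptomatically. On timing, "Only toxicities experienced during the 6 weeks following therapeutic dose administration will be considered as DLT". The Data analysis section restates the rule with no further input.

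Delayed toxicity does appear in the plan. The Secondary objectives section evaluates both acute and delayed toxicity, with special attention to skin, eye and nervous system. The Follow-up section schedules visits at days 14, 28, 42, 63 and 85 after the therapeutic injection. It places the cardiac test at day 85: "Post-therapeutic cardiac evaluation (myocardial perfusion scintigraphy"), which Secondary objectives says includes LVEF. The IDMC section gives the committee safety data and benefit/risk, and has it meet at each DLT or, without DLTs, after every 5 treated patients.

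On which organs might matter, the Discussion notes that "melanin is also present in healthy organs and tissues, as skin (keratinocytes, nævi), eyes (retinal pigment epithelium), brain (basal ganglia), heart" and adipose tissue.

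**The concern.** A 6-week window is a sensible basis for moving the CRM from patient to patient. The difficulty is that the same window also settles the final recommended dose, although later data are planned for every treated patient who stays in follow-up. A fall in LVEF found only by the day-85 test cannot be shown to have occurred within 6 weeks, so in practice it cannot count as a DLT. A silent retinal change that develops after the day-14 examination has no planned examination to reveal it before the window closes.

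The text gives no point at which such findings bear on the dose. Because a late event is not a DLT, it does not by itself trigger an IDMC meeting either. Read literally, the trial could name a recommended dose without anyone being required to look at severe toxicity it has already collected.

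**Working it through.** **Schedule.** Table 2 puts the therapeutic injection at D11, so days after injection = table day − 11: D25 is day 14, D53 is day 42, D74 is day 63, D96 is day 85. These match the visit days in the Follow-up text. The window closes at day 42, and 85 − 42 = 43 days of follow-up lie outside it.

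| Assessment after therapy | Table 2 | Follow-up text | Position relative to week 6 |
|---|---|---|---|
| LVEF | D96 | day 85 | outside |
| Ophthalmologist | D25 (with OCT), D96 | day 14 only | day 14 inside; D96 outside |
| ECG | D53, D96 | not listed separately | day 42 at the edge (±4 days may carry it past); D96 outside |
| Dermatologist | D25, D53, D96 | days 14, 42, 85 | first inside, second at the edge, third outside |
| Neurologist | D25 | day 14 | inside |

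Table and text disagree on whether there is a day-85 eye visit. On either reading, nothing is planned for the eye between day 14 and the end of the window.

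**Patient numbers.** The plan's own figures reproduce: at 50% eligibility, 6/0.5 = 12 and 18/0.5 = 36 patients in the selection part. The number used below is the planned minimum of 6 at the recommended dose.

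**The rule as counts.** The largest count x with x/n < 0.33 is 1 for n = 6, 2 for n = 9, 3 for n = 12 and 5 for n = 18. In each case one more event gives exactly 33.3%. At n = 6, one DLT (1/6 = 16.7%) plus one late event in another patient gives 2/6 = 33.3%; so does no DLT plus two late events.

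**How often this could happen.** Let e be the probability of a DLT by week 6, and l the probability of a first grade 3-4 event from then to day 85 in a patient without a DLT. Both are assumptions. With m the largest passing count,

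P = Σ (x = 0 to m) C(n,x) eˣ (1−e)ⁿ⁻ˣ × P[Bin(n−x, l) ≥ m+1−x].

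For n = 6, m = 1, e = 0.10: P(no DLT) = 0.9⁶ = 0.531 and P(one DLT) = 6 × 0.1 × 0.9⁵ = 0.354, so the dose passes at week 6 with probability 0.886.

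| l | P(≥2 late of 6) | P(≥1 late of 5) | P(passes, then ≥33% by day 85) | True cumulative rate e + (1−e)l |
|---|---|---|---|---|
| 0.05 | 0.033 | 0.226 | 0.531×0.033 + 0.354×0.226 = 0.098 | 14.5% |
| 0.10 | 0.114 | 0.410 | 0.531×0.114 + 0.354×0.410 = 0.206 | 19% |
| 0.20 | 0.345 | 0.672 | 0.531×0.345 + 0.354×0.672 = 0.421 | 28% |

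Over e from 5% to 25% and l from 5% to 20%, the probability runs from 7.7% to 42% at n = 6 and from 4.1% to 44% at n = 9. The calculation takes n at the dose as fixed and does not model CRM allocation.

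**The case against.** Several counter-arguments are sound.

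- A reader might infer that the trial can recommend a dose that fails its own 33% limit. It cannot, on this ground: the limit applies to DLT, and DLT is by definition a 6-week event.
- A reader might also infer that the rule is blind to the heart and the eye. It is not. The day-14 eye examination with OCT lies inside the window, an ECG is planned at day 42, and adverse events are collected throughout, so symptomatic events within 6 weeks count. The gap is confined to toxicity that first arises or is first detected later.
- The documents give no reason to expect frequent late toxicity. The Background reports retinal thinning in mice, but also dosimetric extrapolations suggesting no ocular impact in humans. Treatment requires predicted doses below set limits for liver, kidney, lung and retina (the heart has no such limit). The earlier human series with a related iodine-131 benzamide reported no relevant acute or mid-term toxicity, though in only 9 treated patients. Late rates of 30% or 40% would have no anchor here.
- In all three worked cases the true cumulative rate is below 33%, so 2 of 6 can arise by chance at a tolerable dose. At 10% early and 10% late, a strict day-85 rule would cut acceptance from 0.886 to 0.886 − 0.206 = 0.680. Such a rule would also be exposed to disease progression and to dropout before day 85, and would not match the 6-week basis of CRM allocation. This argues against replacing the primary endpoint, which the documents do not require.
- Delayed toxicity is a secondary endpoint, the IDMC may advise modifying or stopping, and the full protocol may say more than the article. What remains is that the article states the dose rule outright and links no later finding to it.

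**Conclusion.** The point holds as a gap in the decision path. The recommended dose is fixed by 6-week DLT alone, the sole post-treatment LVEF falls 43 days after the window closes, and no stated step requires later grade 3-4 toxicity to be considered before the dose is declared. The consequence is that cumulative severe toxicity to day 85 can stand at or above 33% at a recommended dose. With 6 patients, the chance is about 10%, 21% or 42% for an assumed early rate of 10% and late rates of 5%, 10% or 20%. These illustrate how sensitive a 6-patient rule is and predict nothing about this agent. The 6-week window for escalation and the 33% rule as primary endpoint are not in error; this is a worthwhile, inexpensive improvement.

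**What to change.** Keep the 6-week DLT definition and the 33% rule, both for CRM allocation and as the primary endpoint. In Data analysis, add two sentences to this effect:

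1. For each dose level, the cumulative percentage of treated patients with grade 3-4 toxicity from injection through day 85, with the same exceptions, is reported beside the 6-week DLT percentage. The number actually assessed at day 85 and any attribution to disease progression are shown.
2. The recommended dose is declared only after the IDMC has reviewed these results, including the day-85 LVEF and any day-85 eye findings.

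State the therapeutic population as the denominator. The same section now bases the rule on the "highest tested dose for which the percentage of DLT in the diagnostic population is lower than 33" per cent, and then says "Only therapeutic population will be included in the analysis of DLT and the efficacy analysis"; these two sentences need to agree. Reconcile Table 2 (ophthalmologist at D96) with the Follow-up text (ophthalmologist at day 14 only), since this decides whether any planned day-85 eye data exist.

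The cost is a wording change, one further IDMC review, and a declaration that waits for the last treated patient's already planned day-85 visit, 43 days after that patient's DLT window closes. Late events will need an attribution check.
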